### Eligibility criteria {10}

#### Participants

##### Inclusion criteria

According to the Kidney Disease: Improving Global Outcomes (KDIGO) guidelines, CKD refers to the abnormalities in the kidney structure or function or an estimated glomerular filtration rate (eGFR) of < 60 ml/min/1.73 m^2^ that persists for 3 months with or without kidney damage. The GFR was obtained by calculating the CKD-EPI using the following Cystatin C formula: eGFR=169 × Scr^-0.608^ × CysC^−0.63^ × Age^−0.157^ × (0.83 if female).Patients diagnosed with CKD stages 3–5 (non-dialysis dependent) aged 30–65 years (including those aged 30 and 65 years).Sex and ethnicity restrictions were not imposed.Patients without atherosclerosis in the common carotid artery as observed on the vascular ultrasound examination and no history of atherosclerosis in the carotid artery.An informed consent form from participants is required (Supplementary document).

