### Methods: assignment of interventions

#### Sequence generation {16a}

Central randomization will be used as a randomization method, and the random number will be generated and assigned by the designated data management center. We will use simple randomization for random allocations. Eligible patients will be randomly assigned to the aspirin group or the placebo group. The treatment will last for 36 months.

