### Statistical analysis

#### Statistical methods for primary and secondary outcomes {20a}

For the primary outcome, the chi-square test will be performed to compare the occurrence rate of atherosclerosis at 1, 2, and 3 years of follow-up between the aspirin group and the placebo group. For the secondary outcome, the chi-square test will be performed to compare the combined cardiovascular events and all-cause mortality at 1, 2, and 3 years of follow-up between the aspirin group and the placebo group. Then, the decrease in eGFR will be computed using the value measured at the last follow-up minus the value measured at baseline; patients with a 50% decline in eGFR will be treated as patients who experienced an eGFR reduction of 50%. Similarly, the proportion of patients with an eGFR reduction of 50% between the aspirin group and the placebo group will be compared using the chi-square test. If the previous comparison did not reach a significant difference, the magnitude of decrease in eGFR between the two groups would be compared using two independent sample *t* tests or the Mann-Whitney *U* tests. In addition, multivariate competing-risk regression models will be used to assess the independent effect of treatments adjusted for age, sex, diabetes, serum lipid profiles, and phosphorus.

All statistical analyses will be performed using the SPSS software version 21.0 (IBM Corp., Armonk, NY, USA), and general data will be expressed as mean ± standard deviation. The variables with normal distribution and variance will be compared. One-way analysis of variance will be used for comparisons within groups. The SNK test will be used for multiple comparisons between groups. Pearson’s correlation analysis will be used for analyzing the correlation between variables. A nonparametric test will be used to analyze variables that do not meet the parameter test conditions. The Kruskal-Wallis *H* test or Mann-Whitney *U* test will be used for data comparison. Spearman’s correlation analysis will be used for correlation analysis. The chi-square test will be used for comparison. A *p* value of < 0.05 will be considered significant. A nonparametric test for multiple comparisons will be corrected using the Bonferroni method, *p* < 0.008, statistically significant safety analysis.

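### The comparison of the size of eGFR decrease is not adjusted for baseline eGFR: the test is valid, but it gives up some precision on a conditional secondary analysis.

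*Protocol article*

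**What the plan says.** All of the relevant text is in the protocol article, mostly under Statistical methods for primary and secondary outcomes {20a}.

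- **Variable.** "the decrease in eGFR will be computed using the value measured at the last follow-up minus the value measured at baseline". This is an absolute change.
- **When the test is run.** The proportion with a 50% decline is compared first, by chi-square. The continuous comparison follows only conditionally: "If the previous comparison did not reach a significant difference".
- **Test.** Then "the magnitude of decrease in eGFR between the two groups would be compared using two independent sample" t tests or Mann-Whitney U tests. No covariate is named for either.
- **Only adjusted analysis.** A competing-risk regression assesses the "independent effect of treatments adjusted for age, sex, diabetes, serum lipid profiles, and phosphorus". It models events, not eGFR change.
- **Range at entry.** Inclusion criteria: "Patients diagnosed with CKD stages 3–5 (non-dialysis dependent) aged 30–65 years". Entry eGFR therefore runs from just under 60 down into stage 5.
- **Allocation.** Sequence generation {16a}: "We will use simple randomization for random allocations". Nothing in the design balances CKD stage.

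Baseline eGFR is available for everyone. It decides eligibility, baseline blood is drawn (Collection of basic information), and the change cannot be computed without it.

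**The concern.** A fall in eGFR cannot exceed the starting value. Halving means a loss of 27.5 mL/min/1.73 m² from 55 but only 6 from 12. When entry values are this spread out, part of the variation in raw change may reflect where patients started and not what happened to them. Subtracting baseline removes that part only if follow-up eGFR rises one for one with baseline. Otherwise explainable variation stays in the error term, and the confidence interval is wider than the data require.

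What is at stake is the precision of one kidney comparison. It has some interest because the Discussion cites studies in which 100 mg/day aspirin was associated with more CKD progression. The comparison is also run exactly when the 50%-decline test has been inconclusive.

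**Working it through.** **Inputs.** The article states no SD, correlation, expected decline or power for eGFR, so there is no eGFR figure to reproduce. The only number taken from it is the expected completers: 277 per group less 10% gives about 249 (Sample size {14}). Everything else is assumed and varied.

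**1. General result.** Let s0 and s1 be the SDs of eGFR at baseline and follow-up, and rho their correlation. Per patient:

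- change score variance: s0² + s1² − 2·rho·s0·s1
- variance after adjusting for baseline (ANCOVA): s1²·(1 − rho²)
- difference: (s0 − rho·s1)² = s0²·(1 − b)², where b = rho·s1/s0 is the slope of follow-up on baseline

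The difference is never negative and is zero only at b = 1. So, in large samples, adjustment is never less precise.

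**2. Equal SDs.** The variance ratio, ANCOVA to change score, is (1 + rho)/2. A comparison with 80% power on the change score then has power Φ(2.802/√ratio − 1.96):

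| rho | ratio | power with ANCOVA |
|---|---|---|
| 0.5 | 0.75 | 90% |
| 0.7 | 0.85 | 86% |
| 0.8 | 0.90 | 84% |
| 0.9 | 0.95 | 82% |

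**3. Unequal SDs, rho 0.5 to 0.9.** If s1 = 0.8·s0, the ratio is 0.57 to 0.64. If s1 = 1.2·s0, it is 0.87 to 0.997. At rho = 0.8 in the second case the slope is 0.96, and almost nothing is lost.

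**4. Proportional decline (an assumption).** Let follow-up = B × R, with R lognormal and independent of baseline B, mean m, log-scale SD s. The slope is then m:

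- ANCOVA variance: E[B²]·m²·(exp(s²) − 1)
- change score variance: the same plus (1 − m)²·Var(B)

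For B uniform on 10–59: mean 34.5, Var(B) = 49²/12 = 200.1, E[B²] = 34.5² + 200.1 = 1390.3. For 30–59: mean 44.5, Var(B) = 29²/12 = 70.1, E[B²] = 2050.3. The aspirin arm is given a mean follow-up 8% lower than control (0.92·m).

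*Worked case: 35% loss, s = 0.3, baseline 10–59.*

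- Control m = 0.65, aspirin m = 0.598, exp(0.09) − 1 = 0.0942.
- ANCOVA variances: 55.3 and 46.8. A common slope adds about 0.3, giving a sum of 102.4.
- Extra in the change score: 0.35² × 200.1 = 24.5 and 0.402² × 200.1 = 32.3, giving a sum of 159.0.
- Ratio: 102.4/159.0 = 0.64.
- Difference in means: 0.052 × 34.5 = 1.79.
- SE of change score comparison: √(159.0/249) = 0.80, power about 61%.
- SE of ANCOVA: √(102.4/249) = 0.64, power about 80%.

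The same formulas give the grid below (gains from unrounded powers):

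| baseline | mean loss | s | ratio | power, change | power, ANCOVA | gain (points) |
|---|---|---|---|---|---|---|
| 10–59 | 20% | 0.2 | 0.76 | 95.8% | 98.9% | 3.0 |
| 10–59 | 20% | 0.3 | 0.88 | 74.6% | 79.9% | 5.3 |
| 10–59 | 20% | 0.4 | 0.93 | 51.1% | 54.1% | 2.9 |
| 10–59 | 35% | 0.2 | 0.44 | 80.4% | 98.9% | 18.5 |
| 10–59 | 35% | 0.3 | 0.64 | 61.2% | 79.9% | 18.7 |
| 10–59 | 35% | 0.4 | 0.77 | 44.0% | 54.1% | 10.1 |
| 30–59 | 20% | 0.2 | 0.93 | 99.2% | 99.5% | 0.3 |
| 30–59 | 20% | 0.3 | 0.97 | 83.3% | 84.5% | 1.2 |
| 30–59 | 20% | 0.4 | 0.98 | 58.4% | 59.2% | 0.8 |
| 30–59 | 35% | 0.2 | 0.77 | 97.7% | 99.5% | 1.8 |
| 30–59 | 35% | 0.3 | 0.88 | 79.8% | 84.5% | 4.6 |
| 30–59 | 35% | 0.4 | 0.93 | 56.2% | 59.2% | 2.9 |

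Simulation of the worked case (3,000 replicates) agrees: 62% for the t test, 58% for Mann-Whitney and 80% for ANCOVA. Type I error was about 5% for the change-score test and for ANCOVA.

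**The case against.** The strongest reply is that nothing here is wrong. A two-sample test on change is valid under randomisation and already uses baseline by subtraction. The analysis is a conditional fallback: Table 1 lists the proportion with a 50% decline, not the magnitude. That listed outcome is already relative to each patient's own baseline. The trial is sized only for atherosclerosis and calls itself exploratory and a pilot. The size of the gain also depends on inputs the article does not give. The large gains need both a 35% mean loss and a flat spread of baseline from 10 to 59. With 20% loss, or baseline 30–59, the gain is about 5 points or less. All of this stands, and it makes the point a minor one.

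It does not dispose of the point. Leaving covariates to an unseen analysis plan is a weak defence, because the article names the test. Adjustment costs nothing and cannot lose precision in large samples.

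A reader might infer three stronger things that the article does not support:

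- **Bias from chance imbalance under simple randomisation.** There is none on average. Such imbalance is already in the standard error, so counting it separately counts the same loss of precision twice.
- **Decline known to be proportional, which would require a log scale.** No section says so. It is an assumption of step 4.
- **A defect in the competing-risk covariate list because it omits baseline eGFR.** That model concerns events, and nothing calculated here bears on it.

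**Conclusion.** The point holds as a minor loss of efficiency. The direction is firm: in large samples a baseline-adjusted model is at least as precise as the raw change score, and strictly more precise unless the slope on baseline is 1. The size cannot be derived from the article. With equal SDs the variance ratio is 0.75 to 0.95 for correlations of 0.5 to 0.9, which is like discarding 25% to 5% of the sample for this comparison. Under assumed proportional decline the ratio is about 0.44 to 0.98, and the power gain runs from near zero to about 18–19 points. It is close to zero whenever the slope is near 1.

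The article does not support calling the planned test invalid or biased, or treating this comparison as a main efficacy or harm result. The primary outcome is not affected.

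**What to change.** In Statistical methods {20a}, replace the t or Mann-Whitney test on raw change with a linear model of last-follow-up eGFR on treatment, with baseline eGFR as covariate and robust standard errors. Using change as the response instead gives the same treatment estimate. Prespecify a log-scale or rank-based version for use if the data are skewed. Report the adjusted difference with its 95% confidence interval. This point calls for no change to the competing-risk covariates.

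The cost is wording only. Baseline eGFR is already collected, the named software can fit the model, and no extra patients, visits or assays are needed.

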**Secondary**		
The combined cardiovascular events	Incidence	**36** months
All-cause mortality	Incidence	**36** months
eGFR decreased by 50%	the proportion of eGFR decreased by 50%	**36** months
Safety outcomes	Numbers	**36** months

Carotid ultrasonography will be used to screen for atherosclerosis. The bilateral carotid arteries will be analyzed by color Doppler ultrasound at a frequency of 10 MHz using a linear array transducer (Model Vinno 70; VINNO Technology (Suzhou) Co., Ltd., China) by an experienced sonographer. A smooth carotid artery is considered normal. An atherosclerotic plaque is defined as a focal structure encroaching into the arterial lumen by at least 0.5 mm or 50% of the surrounding intima-media thickness (IMT) value or with a thickness of > 1.5 mm, as measured from the media-adventitia interface to the intima-lumen interface [21]. Both atherosclerotic plaques and IMT are indicators of carotid atherosclerosis. The carotid ultrasonography will be performed at 6, 12, 24, and 36 months to identify the status of carotid atherosclerosis.

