### Data collection and management

#### Plans for assessment and collection of outcomes {18a}

We will use an electronic data collection form to capture the information using pre-existing forms. Participants will be followed up at 0.5, 1, 2, 3, 4, 5, 6, 12, 24, and 36 months. At each follow-up, routine blood tests, blood biochemistry and coagulation, serum lipid levels, and other related tests will be performed. All biochemical indicators, cervical vascular ultrasound, cardiac ultrasound, and electrocardiography will be performed at 6, 12, 24, and 36 months (see the Research flow chart).

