## Discussion

Previous epidemic studies reported that the incidence rates of atherosclerosis in non-diabetic and diabetic CKD patients are 50% and 69%, respectively [16, 22]. The incidence of atherosclerosis in non-diabetic CKD patients was also proven by conducting an imaging analysis in a Korean study, which enrolled more than 3000 individuals without known CAD who underwent coronary computed tomography angiography. This study showed that 34.1% and 48.6% of the individuals with mild (eGFR 60–89 mL/min/1.73 m^2^) and moderate (eGFR 30–59 mL/min/1.73 m^2^) CKD had segment vessel stenosis and stenosis of ≥ 50%, respectively [23]. Aspirin has been shown to improve atherosclerosis in animal models. Aspirin-triggered lipoxins A4 (ATL4) is an effective anti-inflammatory mediator involved in inflammation regression. ATL4 reduced the macrophage infiltration and apoptosis in ApoE−/− mice with atherosclerosis in the aortic roots and thoracic aorta [24]. This indicates that aspirin can inhibit the expression of nuclear factor-kappa B1 and deactivate the cAMP signaling pathway to treat atherosclerosis [25]. Inflammation plays a vital role in the pathophysiology of atherosclerosis, and aspirin has significant anti-inflammatory properties. In Chai et al.’s study, orchidectomized Sprague-Dawley rats fed with a AIN-93 M casein-based control diet for 4 months developed atherosclerotic lesions. After treatment with aspirin (500 mg/kg) for 3 months, the fatty streak area was completely reversed, and the atherosclerotic lesions disappeared [26]. Therefore, the theoretical mechanism and arterial test of aspirin support its role in improving atherosclerosis.

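### The additional adjusted model has a fixed covariate list that omits baseline eGFR, a value already collected, spread over CKD stages 3–5 and not balanced by the simple randomization

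*Protocol article*

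**What the plan says.** All references are to the protocol article.

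- **Primary analysis**, Statistical methods {20a}: "For the primary outcome, the chi-square test will be performed to compare the occurrence rate of atherosclerosis" between the groups. It is unadjusted.
- **Adjusted model**, same section: "In addition, multivariate competing-risk regression models will be used". The purpose given for these models is to "assess the independent effect of treatments adjusted for age, sex, diabetes, serum lipid profiles, and phosphorus". The list is closed. eGFR and IMT are not on it, and no time of measurement is given for lipids or phosphorus.
- **Kidney function at entry**, Inclusion criteria: "Patients diagnosed with CKD stages 3–5 (non-dialysis dependent) aged 30–65 years". The change in eGFR is computed "using the value measured at the last follow-up minus the value measured at baseline", so a baseline value must exist for every patient.
- **Allocation**, Sequence generation {16a}: simple randomization, with no stratification named.
- **Blood tests**, Plans for assessment {18a}: "At each follow-up, routine blood tests, blood biochemistry and coagulation, serum lipid levels, and other related tests will be performed". Collection of basic information also lists baseline blood specimens.
- **Carotid scan**: absence of carotid atherosclerosis on ultrasound is an entry criterion. Outcomes {12} says "Both atherosclerotic plaques and IMT are indicators of carotid atherosclerosis" and schedules scans at 6, 12, 24 and 36 months.

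**The concern.** An adjusted treatment estimate is most useful when it conditions on the strongest baseline predictors that are already to hand. This trial recruits across three CKD stages and counts a halving of eGFR as an outcome, so eGFR at entry is an obvious candidate. The list includes phosphorus but not the direct measure of kidney function, and gives no reason. Because allocation is simple, eGFR is balanced only on average over repeated trials, not within the one that is run.

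At stake is a small amount of information in a supportive analysis, and protection of that analysis against a chance difference in eGFR between the arms. A second, smaller point is that lipids and biochemistry are measured both before and after randomization, and the text does not say which value enters the model.

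**Working it through.** **Inputs.** From Sample size {14}: p0 = 0.40, p1 = 0.25, two-sided α = 0.05, 251 per group before allowance for loss. The documents give no prognostic strength for eGFR, so odds ratios of 1.3, 1.5 and 2.0 per SD are assumed, with eGFR roughly normal after scaling.

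**1. The plan's own figure.** The plan gives no figure for the adjusted model. Its formula for n, with mean rate 0.325, is (1.96·√(2·0.325·0.675) + z_β·√(0.24 + 0.1875))² / 0.15². With z_β = 1.645 this is 250.4, so 251. With the stated β = 0.10 (z_β = 1.282) it is 202.9, so 203. That mismatch is a separate matter. The percentage results in step 3 do not depend on n.

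**2. Crude risk difference.** Variance = (0.24 + 0.1875)/251 = 0.001703; SE = 0.0413; 95% half-width = 1.96 × 0.0413 = 8.1 percentage points.

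**3. Risk difference standardised over baseline eGFR.** With 1:1 allocation and a correct logistic model, the large-sample variance falls by Var(m0 + m1)/(2n), where m0 and m1 are the control and aspirin risks at a given eGFR. The relative fall is Var(m0 + m1) / (2 × 0.4275). Intercepts are set so that the average risks stay at 0.40 and 0.25.

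| Assumed OR per SD | SD of m0 + m1 | Relative fall (formula) | Relative fall (simulation, 251 per arm) |
|---|---|---|---|
| 1.3 | 0.111 | 0.0123/0.855 = 1.4% | 1% |
| 1.5 | 0.168 | 0.0283/0.855 = 3.3% | 4% |
| 2.0 | 0.273 | 0.0746/0.855 = 8.7% | 8% |

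The two columns agree within a percentage point.

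**4. What that buys.** A 1% fall equals 502 × (1/0.99 − 1) ≈ 5 patients, and an 8% fall equals 502 × (1/0.92 − 1) ≈ 44. The half-width goes from 8.1 points to 8.1 × √0.92 ≈ 7.8 at best. These are gains over an unadjusted analysis. The planned model already holds five covariates, so the extra gain from eGFR is smaller to the extent that they track it.

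**5. Chance imbalance.** With 251 per arm, the difference in mean eGFR has standard deviation √(2/251) = 0.089 SD, so differences up to about 1.96 × 0.089 = 0.17 SD are ordinary. On the log odds scale that is 0.17 × ln 1.3 = 0.04 to 0.17 × ln 2.0 = 0.12, against a planned effect of ln[(0.25/0.75)/(0.40/0.60)] = −0.69. This is the loss in step 3 seen from another side, not an extra bias.

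**6. Timing of lipids and phosphorus.** If aspirin shifted a covariate by d SD and the on-treatment value were used, the share of the planned log odds ratio removed would be about d × ln(OR)/0.69. It is 0% at d = 0. At d = 0.1 it is 3% (OR 1.25) to 10% (OR 2.0), and at d = 0.3 it is 10% to 30%. All of these shifts are assumptions.

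**The case against.** The strongest reply is that nothing decisive rests on this model. The primary test is an unadjusted chi-square, the sample size is built on it, and a prespecified covariate list is not an error because another statistician would choose differently. The first part stands in full. The second stands in part: the list is defensible, but leaving out a collected measure that defines the population, without a reason, is a choice that can be bettered for nothing.

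Four stronger readings are tempting and should not be drawn.

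- **That precision is lost in the planned model.** On the log odds scale, adding a prognostic covariate does not shrink the standard error. In simulation it rose from 0.195 to 0.199, 0.206 and 0.219 for odds ratios of 1.5, 2.0 and 3.0 per SD, while the estimate moved further from zero. Power at 251 per arm rose from about 95% to about 96%, 97% and 98%. The variance gain belongs to the standardised risk difference. It was not computed for the competing-risk model.
- **That the plan over-adjusts.** This needs both post-randomization covariate values and an aspirin effect on them, and the article states neither. Its Discussion mentions possible faster CKD progression on low-dose aspirin but does not mention lipids or phosphorus. Baseline values are the ordinary reading, and covariate timing is often left to the analysis plan.
- **That baseline IMT is available.** The entry scan is documented as a check for absence of atherosclerosis. No recorded IMT value is stated.
- **That the Discussion proves eGFR prognostic here.** The sentence beginning "This study showed that 34.1% and 48.6% of the individuals with mild" reports coronary CT angiography, not carotid ultrasound. Its mild group (eGFR 60–89) lies outside the trial's range, and its wording leaves open whether the two percentages share an endpoint. It shows no gradient within stages 3–5.

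**Conclusion.** The point holds as a modest improvement to a supportive analysis. The fixed list omits baseline eGFR, which is collected, varies across stages 3–5 and is not balanced by design. For the standardised 36-month risk difference, the gain from eGFR alone is about 1% to 8% lower variance (8.7% at the top end by the large-sample formula). It rests on assumed odds ratios of 1.3 to 2.0 per SD and on comparison with no adjustment at all; beyond the listed covariates it will be smaller. The primary chi-square result and the sample size do not change. The timing of lipids and phosphorus is a clarification and not a demonstrated fault: over-adjustment arises only if values measured after randomization are used.

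**What to change.** In Statistical methods {20a}:

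1. Add continuous baseline eGFR to the covariates already listed.
2. State that lipids and phosphorus enter at their baseline values.
3. Report a covariate-adjusted (standardised) risk difference for the 36-month primary outcome, with 95% CI, as a supportive analysis beside the crude chi-square comparison.
4. Add baseline IMT only if the entry scan records it. If it does not, recording it would change data collection, and this point does not ask for that.

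Items 1 to 3 are wording and analysis code. They need no new visits, measurements or patients, and should be fixed before unblinding.

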### Trial design {8}

This study is a prospective, open, randomized, controlled multicenter study initiated by the Second Affiliated Hospital of the Army Medical University (Xinqiao Hospital) and approved by the ethics committee of Xinqiao Hospital. An exploratory design will be to investigate the efficacy and safety of aspirin for preventing atherosclerosis in patients with CKD stages 3–5. All eligible patients will be randomly assigned to either the aspirin group or the placebo group (Fig. 1).

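### One-way ANOVA within arms does not fit repeated laboratory values and gives no aspirin–placebo contrast; the SNK test is redundant with two arms (minor)

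*Protocol article*

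**What the plan says.** The protocol's section on statistical methods for primary and secondary outcomes {20a} has two parts.

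The first part gives named outcomes their own methods, all between arms:
- Atherosclerosis: "For the primary outcome, the chi-square test will be performed to compare the occurrence rate of atherosclerosis at 1, 2, and 3 years". Combined cardiovascular events, all-cause mortality and the proportion with a 50% eGFR decline are also compared by chi-square.
- Change in eGFR, if the comparison of proportions is not significant: "the magnitude of decrease in eGFR between the two groups would be compared using two independent sample *t* tests or the Mann-Whitney *U* tests".
- Adjusted analysis: "multivariate competing-risk regression models will be used to assess the independent effect of treatments".

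The second part is general and tied to no endpoint. It states: "One-way analysis of variance will be used for comparisons within groups. The SNK test will be used for multiple comparisons between groups". It then lists Kruskal-Wallis, Mann-Whitney and chi-square tests, and adds: "A nonparametric test for multiple comparisons will be corrected using the Bonferroni method", with a threshold of 0.008.

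Three other statements set the context:
- Trial design {8}: "All eligible patients will be randomly assigned to either the aspirin group or the placebo group".
- Plans for assessment {18a}: "Participants will be followed up at 0.5, 1, 2, 3, 4, 5, 6, 12, 24, and 36 months", and "At each follow-up, routine blood tests, blood biochemistry and coagulation, serum lipid levels, and other related tests will be performed".
- Additional analyses {20b}: no subgroup analysis is pre-defined.

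No repeated-measures or mixed model is named anywhere in the article.

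**The concern.** An ANOVA needs a factor with levels. Inside one arm of a two-arm trial without pre-defined subgroups, the only evident factor is the visit, and the same patients supply the values at every visit. One-way ANOVA assumes that values at different levels come from different people. It therefore leaves the between-patient variance in the error term, and the p value is wrong.

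A test inside one arm also says nothing about aspirin against placebo. If both arms are tested separately and only one is significant, a reader can take that for a treatment effect when there is none.

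The SNK test orders and compares three or more means. Two arms offer one comparison, so it has nothing to do.

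At stake are the repeated laboratory variables (lipids, blood counts, biochemistry, coagulation). This general paragraph is the only place where the article gives them a parametric method.

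**Working it through.** The plan gives no figure for this point, so there is none to reproduce. Three checks follow.

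**1. What the multi-group wording implies**

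Input: two arms (Trial design {8}), hence 2 × 1 / 2 = 1 pairwise comparison.

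- SNK critical value for two groups, on the t scale: studentized range (2 groups, 552 df) / √2 = 1.964. The two-sided 5% t value on 552 df (2 × 277 − 2) is also 1.964. The tests are identical.
- Bonferroni threshold: 0.05 / 6 = 0.0083, close to the stated 0.008. Six is the number of pairs among four groups (4 × 3 / 2). Two arms would give 0.05 / 1 = 0.05. Taken as pairwise comparisons of groups, the threshold belongs to a different design.

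**2. One-way ANOVA across visits within one arm**

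Input from the protocol: 277 patients per arm (Sample size {14}). Assumptions not in the protocol: k = 5 time points (for example baseline, 6, 12, 24 and 36 months), unit variance, compound symmetry with correlation ρ, no missing values.

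Under compound symmetry and no true change, the between-visit mean square has expectation 1 − ρ, while the one-way error mean square has expectation of about 1. The one-way F statistic is therefore about (1 − ρ) times a true F variable, and

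size ≈ P( F(4, 1380) > 2.378 / (1 − ρ) ), where 4 = k − 1, 1380 = 5 × 276, and 2.378 is the 5% critical value.

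| ρ | 2.378 / (1 − ρ) | Size, formula | Size, simulation (4000 runs) | Repeated-measures ANOVA, simulation |
|---|---|---|---|---|
| 0 | 2.38 | 5.0% | 4.6% | 4.5% |
| 0.3 | 3.40 | 0.9% | 1.2% | 4.9% |
| 0.5 | 4.76 | 0.08% | 0.2% | 5.2% |
| 0.7 | 7.93 | below 0.001% | 0% | 4.6% |

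Power for a linear drift of total size s: the visit means deviate from their average by −s/2, −s/4, 0, s/4 and s/2, so the sum of squares is 0.625 s². The non-centrality is 277 × 0.625 s² / (1 − ρ). For s = 0.2 SD this is 6.925 / (1 − ρ); for s = 0.15 SD it is 3.895 / (1 − ρ). One-way ANOVA must exceed 2.378 / (1 − ρ). The repeated-measures test must exceed only 2.380, the 5% value on 4 and 1104 df (4 × 276).

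| ρ | 0.2 SD: one-way vs repeated measures | 0.15 SD: one-way vs repeated measures |
|---|---|---|
| 0.3 | 46% vs 71% | 21% vs 44% |
| 0.5 | 40% vs 86% | 13% vs 59% |
| 0.7 | 30% vs 98% | 5% vs 83% |

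Simulation of the 0.2 SD case gave 48% vs 71%, 39% vs 86% and 29% vs 98%, in agreement.

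**3. Separate tests in each arm**

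Let both arms drift identically, so that there is no treatment effect. If each within-arm test rejects with probability p, exactly one arm is significant with probability 2p(1 − p). With the simulated p for a 0.2 SD drift:

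- ρ = 0.3: 2 × 0.477 × 0.523 = 50% (simulated 50%)
- ρ = 0.5: 2 × 0.388 × 0.612 = 47% (simulated 47%)
- ρ = 0.7: 2 × 0.294 × 0.706 = 42% (simulated 41%)

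With larger common drifts the simulated share falls: 37% to 40% at 0.25 SD and 7% to 15% at 0.3 SD.

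**The case against.** The strongest reply is that no named outcome depends on these sentences. The primary outcome, cardiovascular events, mortality and 50% eGFR decline have between-arm chi-square tests. The size of the eGFR change has a between-arm t or Mann-Whitney test, and a competing-risk model adjusts the treatment effect. The general paragraph itself allows Mann-Whitney and chi-square tests, both usable with two arms. All of this stands. A reader might infer that the plan lacks a treatment comparison, or that ANOVA governs every continuous measure including eGFR and IMT. The protocol does not support either reading. IMT is described as an indicator of carotid atherosclerosis, but Table 1 lists no continuous IMT outcome.

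Second, the paragraph never mentions visits or repeated measures. That is true, and the reading remains an inference. It is the natural one, given two arms, no planned subgroups and laboratory tests at every visit.

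Third, the SNK test is not invalid here. This also stands: with two groups it reproduces the t test and cannot distort a p value.

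Fourth, the power figures concern change over time inside an arm, under assumed correlation and drift. They do not show that any aspirin–placebo comparison goes wrong. Nor does the protocol say that within-arm significance will be read as a treatment effect. It would also go too far to conclude that safety signals will be missed, since adverse events, including laboratory findings, are watched case by case under a separate section {22}.

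None of this makes one-way ANOVA across visits a correct test, or gives the repeated laboratory variables a between-arm estimate.

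**Conclusion.** The point holds as a minor one. As written, the general paragraph prescribes a within-arm test that, on its evident reading, ignores the correlation between visits and yields no aspirin–placebo contrast, together with a between-arm test that has no role with two arms. The error is towards conservatism: a true size of about 1% at ρ = 0.3, falling to practically 0% at ρ = 0.7, instead of 5%. For a 0.2 SD drift the power loss at these correlations is roughly 25 to 70 percentage points.

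These figures rest on five time points, compound symmetry, complete data and the assumed range of ρ. The direction does not depend on the exact ρ: under compound symmetry, any positive correlation makes the one-way test conservative.

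The reach is limited to repeated continuous variables without a method of their own. Nothing here weakens the primary analysis.

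**What to change.** In section {20a}, delete the ANOVA and SNK sentences. Delete also the Kruskal-Wallis test and the Bonferroni threshold of 0.008, which likewise presuppose more than two groups. Keep the chi-square tests, the eGFR-change test and the competing-risk model as they are.

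For the repeated continuous variables without their own method (lipids, blood counts, biochemistry, coagulation), specify one between-arm, baseline-adjusted analysis: a mixed model with arm, visit, arm-by-visit interaction and baseline value, allowing for correlation within patients. Report the aspirin–placebo difference at 36 months with its 95% confidence interval. State that within-arm significance tests will not be used to infer a treatment effect.

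The cost is a change of analysis wording. The planned visits already supply the data, and neither the sample size nor the visit schedule changes.
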